#### Data management and monitoring

All collected data will be stored anonymously and secured at the data centre of Nara Medical University. Only investigators will have access to the data; however, access will be permitted for audits, monitoring, and inspections by concerned authorities. Data monitoring will be performed by a data monitoring committee comprising designated staff who are not involved in the study to ensure accuracy and completion. All collected data will be monitored after the first case and after every 10 cases subsequently. The results will be reported to the investigators in writing, and the investigators will make the final decision regarding trial termination. We do not expect interim analyses, as the possibility of severe adverse events is extremely low.

#### Statistical methods

Baseline characteristics will be summarised as summary statistics (min, median, and max) for continuous variables and as frequency and proportion for binary variables.

For the primary outcome, the difference between the groups will be examined using an unpaired *t*-test. The mean value and its 95% confidence interval of the difference between the groups will be obtained.

Secondary outcomes (i), (ii), (v), (vii), and (viii) will be analysed as follows: the mean and its 95% confidence interval for each time point and group will be estimated. The mean and its 95% confidence interval for the difference between the groups at each time point will be estimated. Secondary outcomes (iv) and (vi) will be analysed as follows: the proportion and its 95% confidence interval for each time point and group will be estimated. The mean and its 95% confidence interval for the difference between the groups at each time point will be estimated. This procedure will be repeated for the cumulative incidence rate using the Kaplan–Meier method, if necessary.

Exploratory analysis of the relationship between NOL and NR will mainly be performed using correlation coefficients and some plots.

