### Primary and secondary outcomes

The primary outcome is the mean intraoperative remifentanil infusion rate per ideal body weight (IBW). The infusion rate will be calculated as total amount of intraoperative remifentanil divided by the duration of the surgery, and IBW will be calculated as 22 × (height in metres).^2^

Plasma inflammatory biomarker concentrations, including IL-6 and CRP, will be compared between the groups as secondary outcomes. The time points for the assessment of these biomarkers were selected based on previous studies,^6^^,^^8^ which showed that IL-6 concentrations increased 0–2 h postoperatively and peaked at 12–24 h postoperatively, whereas CRP concentrations showed a delayed peak at 1–3 days postoperatively. As in previous studies,^3^^,^^6^ we will measure cortisol concentrations at baseline and at the end of surgery.

Variations in the NOL index at the start of pneumoperitoneum and in response to postural changes will be investigated as secondary outcomes. These sub-analyses will provide information on the clinical limitations of anaesthetic management using the NOL index.

The secondary outcomes include the following: (i) perioperative IL-6, CRP, and cortisol concentrations (IL-6 and cortisol will be assessed by electrochemiluminescence immunoassay); (ii) total remifentanil dose; (iii) variation from baseline in the NOL index 60–90 s after each of tracheal intubation, the onset of pneumoperitoneum, and any postural changes; (iv) postoperative pain score (numeric rating scale [NRS]) 2 h after surgery and on postoperative Days 1, 2, 3, and 7; (v) incidence of postoperative nausea and vomiting (PONV) 2 h after surgery and on postoperative Days 1, 2, and 3; (vi) dose of postoperative opioid fentanyl and analgesic agents; (vii) occurrence of chronic pain at 3 months postoperatively; (viii) dose of vasoactive agents (phenylephrine, ephedrine, norepinephrine, and atropine); (ix) duration of hypotension (MAP below 60 mm Hg), hypertension (systolic BP over 160 mm Hg), bradycardia (heart rate less than 40 beats min^−1^), and tachycardia (heart rate more than 100 beats min^−1^).

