Several blood samples will be collected to evaluate the concentrations of the biomarkers (Fig. 3). The time points of blood sampling, including routine care for the procedure, are several days before surgery (–*t*^1^), after induction of anaesthesia (*t*^1^), after the procedure (*t*^3^), on postoperative Day 1 (*f*^1^), and on postoperative Day 3 (*f*^3^). IL-6 will be measured at *t*^1^, *t*^3^, and *f*^1^; CRP at –*t*^1^, *f*^1^, and *f*^3^; and cortisol at *t*^1^ and *t*^3^.

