### Sample size calculation

The sample size was calculated based on a previous meta-analysis^14^ that found NOL-guided analgesia protocols to decrease intraoperative remifentanil consumption (standardised mean difference [SMD] –0.68; 95% confidence interval: –1.13 to 0.24; *P*=0.003). We will focus on one disease and procedure and the NOL index alone in the present trial, and thus, we expect less variability. Accordingly, we estimated SMD as 0.8 to obtain group sample sizes of 25 patients achieving 80% power with a significance level of 0.05. Considering a dropout rate of 10%, we will enrol 27 patients in each group.

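### Comparing IL-6, CRP and cortisol as raw means, without a log scale or baseline covariate, is unbiased but probably gives up power on the stress-response question

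*Protocol article*

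**What the plan says.** Secondary outcome (i) in the protocol article is defined simply as "perioperative IL-6, CRP, and cortisol concentrations". Statistical methods assigns it a fixed analysis: "the mean and its 95% confidence interval for each time point and group will be estimated", and then "The mean and its 95% confidence interval for the difference between the groups at each time point will be estimated". No covariate, change score, transformation or geometric mean is named.

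The blood-sampling paragraph under Primary and secondary outcomes gives every marker an early sample:

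- IL-6: t1, t3 and f1.
- CRP: –t1, f1 and f3.
- Cortisol: t1 and t3.

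Here –t1 is several days before surgery, t1 is after induction, t3 is after the procedure, and f1 and f3 are postoperative days 1 and 3. For cortisol the early sample is called a baseline: "we will measure cortisol concentrations at baseline and at the end of surgery". By contrast, outcome (iii) is defined relative to its baseline: "variation from baseline in the NOL index 60–90 s after each of tracheal intubation".

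**The concern.** The abstract and introduction motivate the trial partly by an earlier report that NOL-directed dosing might raise the stress response, and the biomarkers are measured to look for that. The sample size is set on remifentanil only; no precision is stated for the biomarkers.

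If IL-6 and CRP are right-skewed, a few high values dominate a difference in raw means with about 25 per arm. If later values track the early value, leaving it out of the model leaves removable noise in the comparison. Either way the interval is wider than the data require. On a question about unintended harm, an imprecise null result is easily read as reassurance.

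**Working it through.** **The plan's own figure.** Sample size calculation: "we estimated SMD as 0.8 to obtain group sample sizes of 25 patients achieving 80% power with a significance level of 0.05". The normal approximation gives n = 2(1.960 + 0.842)² / 0.8² = 24.5, so 25 per group, as stated. With 27 enrolled and 10% dropout, 27 × 0.9 = 24.3, so 25 per arm is a fair number to use below.

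**Inputs not in the article.** No SD, skewness or baseline correlation is given for any marker. Assumed: lognormal concentrations, log-SD s from 0.6 to 1.0, and correlation r between log baseline and log follow-up of 0, 0.3 or 0.5.

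**Power by formula, log scale.** The non-centrality is ln(ratio) / (s√(2/n)). For a 1.75-fold rise at s = 0.8 and n = 25:

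- ln 1.75 = 0.560 and 0.8 × √0.08 = 0.226, so the non-centrality is 2.47.
- Power ≈ Φ(2.47 − 2.01) = 68%.
- ANCOVA divides the standard error by 1/√(1 − r²) and pays a small-sample factor √(1 + 1/46) = 1.011. At r = 0.5 the non-centrality is 2.47 / (0.866 × 1.011) = 2.82, and power ≈ Φ(2.82 − 2.01) = 79%. At r = 0.3 it is 71%; at r = 0 it is 67%.

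**Power by simulation** (20,000 to 40,000 replicates, 25 per arm; repeat runs agree within about 1 point):

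| log-SD | True ratio | Raw means | Log scale | Log ANCOVA, r = 0 | r = 0.3 | r = 0.5 |
|---|---|---|---|---|---|---|
| 0.6 | 1.5 | 58% | 65% | 64% | 68% | 76% |
| 0.8 | 1.5 | 33% | 42% | 41% | 44% | 52% |
| 0.8 | 1.75 | 56% | 68% | 67% | 71% | 79% |
| 1.0 | 2 | 49% | 67% | 66% | 70% | 79% |

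The log scale alone adds 7, 9, 12 and 18 points. Adjustment then adds about 3 points at r = 0.3 and 9 to 12 at r = 0.5, and costs about 1 at r = 0.

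**Interval width from adjustment alone.** Relative to no adjustment, with the small-sample cost included: 1.01 at r = 0, 0.99 at r = 0.2, 0.97 at r = 0.3 and 0.88 at r = 0.5. A simple change score would not be a good substitute: its variance ratio is 2(1 − r), which is 1.4 at r = 0.3 and only reaches 1.0 at r = 0.5.

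**Coverage of the planned raw-scale 95% intervals** (simulation):

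- One group's mean: 92.6%, 90.5% and 87.5% at log-SD 0.6, 0.8 and 1.0, with most misses on the low side.
- Between-arm difference: about 96% with no effect, 95% at ratio 1.5, and 92 to 94% at ratio 2.

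**Status of the early samples.** Allocation says the anaesthesiologist opens the envelope before the operation. The NOL group section fixes the opioids given at induction; the Control group section leaves dosing to the anaesthesiologist. The t1 sample comes after induction, so for IL-6 and cortisol it is taken after randomisation and may already be affected by arm. Only CRP at –t1 is clearly a pre-treatment value.

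**The case against.** The strongest reply is that this is a condensed article on secondary outcomes, that a fuller plan may add covariates or a log scale, and that every magnitude above is assumed. The last part stands. If the post-induction IL-6 value barely predicts the surgical response, adjustment gains nothing; if the markers are nearly symmetric, the log scale gains little. The first part carries less weight, because the article does state a method for outcome (i), and a better one would have to replace it.

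Three stronger readings are tempting, and the documents do not support them.

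- A reader might infer that the between-arm intervals are invalid. They are not: their coverage stays near nominal. Only the per-group intervals under-cover, at about 88 to 93%.
- A reader might infer that chance baseline imbalance biases the result. Randomisation protects against that, and the unadjusted interval already allows for chance. The early values are also not ignored, since means at every time point would include them.
- A reader might infer that all three markers should be adjusted for their early value as the main analysis. For IL-6 and cortisol that could remove part of the effect being sought, so an unadjusted main comparison is defensible there.

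It would also go too far to call the stress response the trial's main aim: the primary outcome and sample size concern remifentanil.

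**Conclusion.** The point holds as one of efficiency. The stated analysis of the biomarkers is valid under randomisation but likely to be less powerful than it could be. Under lognormal data with log-SD 0.6 to 1.0 and 25 per arm, the log scale recovers about 7 to 18 points of power. Baseline adjustment is worth about 3 points at r = 0.3 and 9 to 12 at r = 0.5, with a loss of about 1 if there is no correlation.

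The benefit differs by marker. CRP can gain from both changes. IL-6 gains mainly from the log scale, because its adjusted result should be supportive only. For cortisol no skewness is argued, and its main comparison stays as planned. The primary analysis is untouched.

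**What to change.** In Statistical methods, separate the biomarkers from the other outcomes that share their analysis:

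- **IL-6 and CRP:** compare arms on the log scale at each postoperative time point and report geometric mean ratios with 95% confidence intervals. Keep raw means and medians as description.
- **CRP:** use ANCOVA on log concentration with arm and log –t1 value.
- **IL-6 and cortisol:** keep the comparison not adjusted for t1 as the main result and show the t1-adjusted result alongside, stating that t1 follows induction and may be affected by arm.

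No extra samples, visits or patients are needed. The cost is that IL-6 and CRP results read as ratios instead of absolute differences. That changes the quantity estimated, so it should be fixed before the outcome data are examined.

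### The outcome numerals in the analysis section do not match the outcome list: pain score and postoperative analgesic dose are assigned proportions, and correcting the apparent one-place shift still leaves pain score and NOL variation without a method

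*Protocol article*

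**What the plan says.** The section Primary and secondary outcomes of the protocol article numbers the secondary outcomes (i) to (ix). Those that matter most here are "iii) variation from baseline in the NOL index 60–90 s after each of tracheal intubation" and two other events, the pain numeric rating scale (NRS) as (iv), "v) incidence of postoperative nausea and vomiting (PONV) 2 h after surgery" and on later days, and "vi) dose of postoperative opioid fentanyl and analgesic agents; (vii) occurrence of chronic pain at 3 months postoperatively". The list ends with vasoactive doses (viii) and durations of hypotension, hypertension, bradycardia and tachycardia (ix).

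Statistical methods then refers to these outcomes by numeral only, in two blocks:

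- Mean block: "Secondary outcomes (i), (ii), (v), (vii), and (viii) will be analysed as follows: the mean and its 95% confidence interval", followed by a mean difference between groups at each time point.
- Proportion block: "Secondary outcomes (iv) and (vi) will be analysed as follows: the proportion and its 95% confidence interval", followed by the same sentence about a mean difference. It closes with "This procedure will be repeated for the cumulative incidence rate using the Kaplan–Meier method, if necessary".

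The rest of that section covers baseline characteristics, the primary outcome and the exploratory relation between NOL and the nociceptive response. None of it covers (iii) or (ix).

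**The concern.** A numeric score and a drug dose cannot be reported as proportions unless a threshold turns them into yes/no variables, and the article states none. Conversely, two yes/no outcomes are placed under means. An analyst who follows the numerals literally would produce nothing interpretable for postoperative pain or postoperative analgesic consumption. Both bear on the trial's rationale, since the introduction cites lower postoperative pain scores as a benefit of NOL guidance. NOL variation, which the abstract names as a secondary outcome, is not assigned to either block.

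**Working it through.** The plan gives no figure on this point, so the check is an item-by-item comparison of the two sections.

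**Step 1. Numerals as printed**

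| Outcome | Content | Type | Assigned summary | Fit |
|---|---|---|---|---|
| (i) | IL-6, CRP, cortisol | continuous | mean | yes |
| (ii) | total remifentanil dose | continuous | mean | yes |
| (iii) | NOL variation | continuous | none | – |
| (iv) | pain NRS | numeric score | proportion | no |
| (v) | PONV incidence | yes/no | mean | no (mild) |
| (vi) | postoperative fentanyl and analgesic dose | continuous | proportion | no |
| (vii) | chronic pain at 3 months | yes/no | mean | no (mild) |
| (viii) | vasoactive dose | continuous | mean | yes |
| (ix) | duration of haemodynamic events | continuous | none | – |

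Count: 3 fit + 4 of the wrong type + 2 unassigned = 9. Of the 7 outcomes that are assigned, 4 do not fit.

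**Step 2. How serious is each mismatch?** For (v) and (vii) the point estimate survives, because the mean of a 0/1 variable is the proportion and the difference in means is the risk difference. For (iv) and (vi) no such rescue exists: without a cut-off there is no proportion to estimate. So two of the four mismatches are substantive and two are largely a matter of labels.

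**Step 3. Is there a pattern?** Remove (iii) and move each later item up one place:

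| Shifted numeral | Content | Printed assignment | Fit |
|---|---|---|---|
| (i) | biomarkers | mean | yes |
| (ii) | remifentanil dose | mean | yes |
| (iii) | pain NRS | none | – |
| (iv) | PONV | proportion | yes |
| (v) | postoperative fentanyl and analgesic dose | mean | yes |
| (vi) | chronic pain | proportion | yes |
| (vii) | vasoactive dose | mean | yes |
| (viii) | duration of events | mean | yes |

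All 7 assigned numerals now fit, and the durations gain a mean. Two outcomes remain without a method: the pain NRS and the removed item, NOL variation.

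**Step 4. The closing sentences of the proportion block.** As printed, the Kaplan–Meier step attaches to a score and a dose, neither of which has an event time. On the shifted reading it attaches to PONV and chronic pain. PONV is assessed at 2 h and on Days 1, 2 and 3, so a cumulative incidence has meaning there. Chronic pain is listed at a single time, 3 months, so nothing accumulates. The repeated mean-difference wording is also wrong for a block about proportions, where the contrast is a risk difference.

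**The case against.** The strongest defence is that this is a visible numbering slip in a condensed article. The full protocol or the SAP, neither of which is shown, may carry the correct mapping, and outcome type leaves little doubt which summary was meant for most items. The primary analysis and the sample size do not depend on it, and the secondary outcomes are assigned estimates with intervals and no hypothesis tests. Much of this stands, and it limits the severity. It does not remove the point, because the printed text positively assigns the wrong summaries, and repairing the slip does not yield a method for (iii) or (iv).

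Several stronger readings are tempting but not supported:

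- A reader might infer that six of nine secondary analyses are equally broken. They are not: (v) and (vii) keep the right point estimate, and (ix) has a mean once the shift is undone. The absence of (iii) and (ix) from the lists, taken alone, is something an article may leave to the SAP.
- A reader might infer that estimators will be chosen after the data are seen. That cannot be shown while the SAP is unseen.
- A reader might infer impossible confidence limits for PONV. With an assumed 2 of 25 patients, a t-interval has standard error √(0.08 × 0.92 × 25/24)/5 = 0.0554 and limits 0.08 ± 2.064 × 0.0554, about −3% to 19%. But the article names no interval method for the secondary outcomes, so this rests on an assumed count and an assumed method. It shows no defect in the text.
- A reader might infer that Kaplan–Meier is misplaced altogether. The sentence is conditional, and for PONV it comes close to the simple proportion with any PONV up to Day 3.

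**Conclusion.** The point holds as a cross-reference error with two real gaps behind it. As printed, the summaries for the pain NRS (iv) and the postoperative analgesic dose (vi) are undefined, those for PONV (v) and chronic pain (vii) are mislabelled, and (iii) and (ix) are unassigned. A one-place shift after (ii) explains all four mismatches and the loss of (ix). That cause is inferred from the pattern; the article does not state it. With the shift undone, NOL variation and the pain NRS still have no stated analysis. This should be fixed before analysis. It is not critical, because the primary outcome, its t-test and the sample size are untouched. The conclusion rests only on comparing the two sections of the article and on the absence of any stated cut-off for (iv) or (vi).

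**What to change.** Rewrite the two blocks by outcome name instead of numeral:

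- Mean with 95% CI of the between-group difference: biomarkers (i), total remifentanil dose (ii), postoperative fentanyl and analgesic dose (vi), vasoactive dose (viii), duration of haemodynamic events (ix).
- Proportion and risk difference with 95% CI: PONV (v) and chronic pain (vii). Replace the mean-difference wording in this block.
- NOL variation (iii) and pain NRS (iv): state a method, for example mean and 95% CI at each time point. For (iii), also say whether a between-group comparison is intended, since the article describes this work as sub-analyses on the limitations of the index.
- Cumulative incidence: tie the sentence to PONV only, for example any PONV up to postoperative Day 3, or delete it.

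If the full protocol or SAP already has the correct mapping, bring the published text into line with it. The cost is wording only, with no change to data collection, sample size or the primary analysis.

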### Harms

The intervention is wearing a finger probe similar to a pulse oximetry probe, which is not associated with complications.

We will take intraoperative blood samples from the arterial line, which is routinely placed during surgery, and take postoperative blood samples during the course of routine postoperative care. As the additional volume of collected blood is minimal, it will not affect the condition of the patients.

The NOL-guided protocol may cause excessive or insufficient analgesia because the remifentanil infusion rate will be determined solely by the NOL in the intervention group. However, meta-analyses reported that nociception monitoring does not increase intraoperative opioid consumption,^14^, ^15^, ^16^ and we will avoid insufficient analgesia by maintaining a remifentanil infusion rate >0.1 μg kg^−1^ min^−1^.^4^

## Dissemination plans

Dissemination plans include presentations in peer-reviewed scientific journals and at international conferences.

### Ethics and dissemination

#### Ethics approval

The study protocol was approved by the Certified Review Board of Nara Medical University on May 11, 2022 (CRB5200002). This study will be conducted in accordance with the Declaration of Helsinki and adhere to the Clinical Trial Act. Written informed consent will be obtained from all individual participants included in this study by investigators. No individual person's data will be used for this study.

### Protocol amendments

If the study protocol requires amendment, all of the content of the revision and its reasons will be reported to the institutional ethics committee. After the re-examination and approval, the investigators will revise the instructions for patients.

### Ancillary and post-trial care

There is no post-trial care in this protocol. The investigator will have insurance to compensate the participants for any harm related to this trial.

